### Collection and storage of biomaterials

At each appointment, biomaterials from mothers (breast milk) and child (nasal brushes, pharyngeal swabs, skin swabs, stool, blood) are collected according to the schedule illustrated in **Figure 3**. We have chosen these timepoints to afford serial profiling while minimizing burden. Collection and storage of biomaterials are performed according to established standard operating procedures (SOPs). After collection, biomaterials are immediately transferred to the adjacent laboratory for processing and biobanking.

**Figure 3 f3:**
[figure not shown]
Collection of biomaterials in MIAI. Biomaterials collected in the MIAI cohort include breast milk, nasal brushes and secretions, pharyngeal swabs, skin swabs, stool, cord blood and peripheral blood (EDTA and serum). They are obtained at the defined study time points, i.e. either at day 1-3 and/or day 30 of life and/or at 6 months and/or 1 year following birth. (Created with BioRender.com).

#### Breast milk samples

As long as the mother is breastfeeding, breast milk/colostrum are sampled at each appointment. First, cells are pelleted by centrifugation and the skim milk and the fat layer are removed. The skim milk and fat layer are once more sharply centrifuged and aliquoted for storage at -80°C for later proteomic and microbial studies. The cells are cryopreserved at -152°C in RPMI 1640 with 20% fetal calf serum (FCS) and 10% dimethyl sulfoxide (DMSO) (all Sigma-Aldrich, Darmstadt, Germany) following multiple washing steps for later single cell studies.

#### Nasal brushes

Nasal brushing is an established method in pediatric pulmonology, e.g. essential for diagnosing primary ciliary dyskinesia, and provides a robust technique to generate airway epithelial cell (AEC) cultures in term and even preterm infants (21, 42). Brushings are taken from the inferior nasal turbinate using sterile interdental brushes (Rossmann, ISO sizes 4 or 5). After sampling, brushes are immediately placed in sterile tubes with transport medium (MEM without additives, antibiotics and antimycotics) and processed within 1 h of collection. Brushes are carefully moved up and down to scrape the cells off and collect them into the transport medium. Next, cells are centrifuged and supernatants stored as “nasal secretions” at -80°C for later proteomic, cytokine and microbiota profiling. The AECs are first expanded in submersion according to established protocols (43, 44) and then cryopreserved at -152°C in BEGM medium (Lonza, Basel, Schweiz, Switzerland) with 20% FCS and 10% DMSO. Some of the expanded AECs are directly differentiated at the air-liquid-interface (ALI) into a mature pseudostratified respiratory epithelium as described previously (44) and used for infection experiments with RSV (RSV-A-ON1, HRSV/A/DEU/H1/2013) (45) and IAV (H1N1, A/Netherlands/602/2009). Infections with SARS-CoV-2 (SARS-CoV-2/human/DEU/REGS-200701-CA/2020) are done later under biosafety level 3 conditions using cryopreserved AECs for differentiation at ALI. After infection, AECs are harvested and subjected to immediate flow cytometry studies capturing cell composition and cell quality, generation of total RNA lysates for the analysis of transcriptomes (bulk RNASeq) and viral loads (qRT-PCR), and standardized cryopreservation (46) for later single cell (scRNASeq) and epigenetic (ATACSeq) studies. Apical and basolateral supernatants are stored at -80°C for later analyses of proteome (mass spectrometry) and cytokine (FACS-based multiplex assays) profiles and virus plaque assays assessing viral progeny. This approach aims at generating data from each MIAI participant regarding individual airway epithelial immune responsiveness and function toward RVIs at birth and at 1 year of life (**Figure 3**). The strategy is based on previous reports that ALI-AEC models established from human primary AECs recapitulate well the *in vivo* phenotype of the airway epithelium (21, 47, 48).

#### Pharyngeal and skin swabs

Three pharyngeal swabs and two skin swabs are collected, respectively. One of the respective swabs is transferred to a sterile tube containing sterile PBS with 10% BSA (for protein stabilization) and stored at -80°C for protein and cytokine measurements. The other two respective swabs are stored at -80°C without additives for later DNA isolation and microbiota studies (16S rRNA sequencing and shotgun metagenomics).

#### Stool samples

Stool samples are collected by the MIAI staff from diapers and immediately transferred to -80°C. In cases where stool collection at the respective appointments not succeeds, we use samples collected and stored at 4°C by the parents at the evening before or the morning of the follow-up appointment for biobanking at -80°C. Three 1.5 ml tubes are filled with stool, respectively, one of which contains 600 µl DNA/RNA shield (Zymo Research, California, USA) to preserve nucleic acids for 16S rRNA sequencing and metagenomics studies. The other two stool aliquots are stored without additives and used for the extraction and analysis of immunoactive proteins such as S100-alarmins (49) and cytokine profiles according to established protocols (50).

#### Blood samples

Cord blood is collected preemptively from all eligible neonates but only processed when parents agree on participation in the MIAI study. If no consent is given, cord blood samples are discarded. The volumes of drawn peripheral venous blood samples align to the pediatric guidelines of the European Medical Agency, which recommends that blood collection for research purposes should be at maximum 1% of total blood volume (i.e., 0.8 ml/kg body weight). At the first sampling timepoint, we seek to combine blood collection in MIAI with the routine newborn screening taken between 36 and 72 hours of life. Blood samples are processed within 1 h after collection. After blood clotting, serum samples collected in serum separator tubes are centrifuged at room temperature 1,800 x g for 10 minutes and stored in two aliquots at -80°C and used for cytokine and metabolome studies (high-resolution mass spectrometry) and serological studies including quantification of antibody titers against RSV, IAV and SARS-CoV-2. From EDTA samples, peripheral blood mononuclear cells (PBMCs) are isolated by Ficoll-Paque PLUS (Sigma-Aldrich) density gradient centrifugation and profiled using established multidimensional flow cytometry panels (51–55). One part of isolated PBMCs is cryopreserved at -152°C in RPMI 1640 with 20% FCS and 10% DMSO for later single cell, epigenetic and experimental studies (e.g., analysis of T and B cell subsets and receptor repertoires including virus-specific effector T cells). To avoid functional impairment of the myeloid cells due to cryopreservation, monocytes are directly isolated from the other part of isolated PBMCs as described previously (11, 56) and infected with RSV and IAV. After infection, total RNA lysates are generated and culture supernatants harvested and both stored at -80°C for the analysis of transcriptomes, viral loads, proteome and cytokine profiles, and viral progeny.

### Sample analysis strategy

Due to the longitudinal nature of the study, exceeding differences in the sample storage times that could give rise to data variability and bias ideally should be avoided. Moreover, exceeding storage times in principle need to be prevented due to potential degradation over time depending on the nature of the biological material and the intended downstream application. Our sample analysis strategy adheres to the standards of the International Society for Biological and Environmental Repositories (ISBER) and the Biobanking and BioMolecular resources Research Infrastructure (BBMRI-ERIC). Samples stored at -80°C that will be subjected to proteomic and cytokine studies (skim milk supernatants, nasal and pharyngeal secretions, skin swabs, stool and serum samples, and cell culture supernatants from AEC and monocyte infection models) are usually stable for several years to decades. At least two aliquots are prepared to avoid freeze-thaw cycles. Likewise, samples collected for microbiome studies (skim milk supernatants, nasal and pharyngeal secretions, skin swabs, and stool samples) can be stored for several years at -80°C. After DNA isolation, samples are directly subjected to library preparation and sequencing. Likewise, RNA lysates in RNAlater generated from AEC and monocyte cell culture infection models can be stored for years at -80°C while RNA is only isolated and libraries prepared shortly before bulk RNAseq is appointed. Cryopreserves (breast milk cells, AECs, and PBMCs) are stored at -152°C in a highly standardized manner ensuring cell viability for several years and high quality for later single cell studies like scRNAseq.

In principle, samples stored for subsequent generation of big omics datasets in batches (e.g., transcriptomics, proteomics, metabolomics, microbiomics) are processed when full series from *n*=100 individuals have been collected and when the storage time of the most recently stored samples is 6 months. With a current recruitment rate of 6 children per month this strategy ensures the analysis of full series from n=100 children within 2.8 years (calculated from the date on which the first patient of each batch has been recruited and sampled). This comes with differences in storage times between d1-3 samples and 1-year samples but needed to be weighed against the batch effects that result from analyzing samples at too many different time points. Based on our experiences in multiple different cohorts we evaluated the latter more considerable. The 6-months storage quarantine is a strategy to mitigate the storage time differences by subjecting 1-year samples at least to a significant storage time to become more comparable to d1-3 samples. Nevertheless, the sample storage time is definitely handled as potential covariate and is as such integral part of each data analysis pipeline used in MIAI.

### Data analysis and statistics

Omics data analysis in MIAI will be performed on different levels as results from flow cytometrics, transcriptomics including lymphocyte receptor repertoires, epigenomics, 16S rRNA gene and shot-gun metagenomics sequencing, breast milk and serum metabolomics and proteomics including cytokine and serologic profiles. We aim at subjecting full longitudinal sample series from 400 infants to study the omics profiles. Given the longitudinal nature of our study set up, stored samples previewed for sequencing, proteomic and metabolomic studies will be randomized to reduce batch effects. Initially, each omics dataset will undergo individual analysis to elucidate its unique characteristics. Flow cytometry data are acquired with an Attune CytPix Flow Cytometer using the Attune Cytometric Software version 6.0 (Thermo Fisher Scientific) and then subjected in batches to analyses using the Pytometry (57) and cyCONDOR (58) pipeline. Subsequent exploratory analyses will determine the necessity of batch correction for each dataset. If required, corrections will be implemented using ComBat batch method to normalize across multiple analytical runs and WithinVariation function implemented in the R mixOmics package and to normalize features as change over time within each child. Post-correction, we will validate that the biological variability is preserved and that no artifacts were introduced. We will perform omics-specific statistical analyses and co-expression network analyses using hCoCena (59, 60) to identify and characterize differential subgroups with greater precision. All data generated including standardized meta-data will be quality-controlled and gathered within a unified framework following standards for omics and clinical measurement representation, allowing within-study integration and comparative analysis with previous studies according to FAIR data principles.

Differential trajectorial endotypes will be identified using KmL (k-means for longitudinal data) clustering. To determine the optimal number of clusters (k), we will run 1000 permutations, utilizing the Harabasz criterion (Calinski-Harabasz index) to evaluate clustering validity. This methodology will facilitate a nuanced, continuous classification of patients, transcending binary categorization and allowing also for a more detailed representation of endotypic variation. Specialized software packages for dataset-specific imputation will be employed to address any missing data points, ensuring robust classification of immune and microbiome trajectories across the cohort. Advanced statistical methods and machine learning algorithms will be integrated into the analysis pipeline to enhance the precision and reliability of the endotype classification.

To elucidate the relationships between specific immunotypes, respiratory or gut microbiome profiles, environmental factors, and clinical outcomes, we have created two specialized software tools, metadeconfoundR (61) and longdat (62). These tools enable comprehensive mixed omics data analysis while managing the complex interplay of numerous demographic, therapeutic, and disease-related variables. MetadeconfoundR is designed to facilitate the identification of biomarkers within cross-sectional multi-omics medical datasets, while carefully accounting for confounders. Initially, it identifies significant associations between features and metadata using nonparametric tests such as the Mann-Whitney U test. Subsequently, it assesses and adjusts for confounding effects among these metadata variables through *post-hoc* nested linear model comparison. Importantly, metadeconfoundR can integrate previously established knowledge of confounders, such as drug associations from the MetaCardis cohort, into its analysis. This inclusion aids in maintaining robust conclusions even when new datasets lack the statistical power to independently identify these confounders. LongDat, meanwhile, is an R package tailored for analyzing longitudinal multivariable data, effectively handling a wide array of covariates. It distinguishes direct from indirect intervention effects and identifies key covariates that may act as mechanistic intermediates. Although primarily focused on longitudinal microbiome data, LongDat’s versatility allows application to various data types including binary, categorical, and continuous data. Comparative testing against other analytical tools like MaAsLin2, ANCOM, lgpr, and ZIBR has demonstrated LongDat’s superior performance in terms of accuracy, runtime, and memory efficiency, making it an ideal choice for high-dimensional longitudinal studies where multiple covariates are a consideration.

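### If 16S or metagenomic data need batch correction, the only across-run method named is ComBat, which splits tied zeros by run and weakens a between-child rank screen for sparse taxa

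*Protocol article*

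**What the plan says.** All of the following is in the protocol article, Data analysis and statistics, unless stated otherwise.

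- The omics layers include "16S rRNA gene and shot-gun metagenomics sequencing, breast milk and serum metabolomics and proteomics including cytokine and serologic profiles".
- Correction is conditional: "Subsequent exploratory analyses will determine the necessity of batch correction for each dataset". If it is needed, "corrections will be implemented using ComBat batch method to normalize across multiple analytical runs". The same sentence adds the "WithinVariation function implemented in the R mixOmics package and to normalize features as change over time within each child".
- No layer is exempted. No count-based or zero-preserving variant is named, and no data scale is given for the microbiome tables.
- A safeguard follows: "Post-correction, we will validate that the biological variability is preserved and that no artifacts were introduced". It has no criterion and no alternative method if the check fails.
- Before measurement, "stored samples previewed for sequencing, proteomic and metabolomic studies will be randomized to reduce batch effects".
- The cross-sectional tool, metadeconfoundR, first screens features against metadata with "nonparametric tests such as the Mann-Whitney U test" and then compares nested linear models to handle confounding among metadata variables. LongDat is the longitudinal tool.
- Sample analysis strategy: stored samples are processed once full series from 100 children are complete. The target is 400 infants, and recruitment runs at 6 per month.

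**The concern.** ComBat shifts and scales each feature within each run under a normal model. That suits roughly continuous measurements. Infant 16S and metagenomic tables hold many zeros, and all samples that lack a taxon share one value. After ComBat they share a value only within a run. The differences between runs may be tiny, but a rank test sees only order and treats them as full separation.

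At stake is the between-child screening of microbiome features, which feeds Aim 3. A sparse taxon with a true association may be missed at the screen, and the later nested-model step does not recover a taxon that was never flagged. If an exposure is commoner in some runs than in others, run-ordered zeros can also look like an association.

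**Working it through.** **1. Number of runs.** 400 / 100 = 4 processing batches at least. The article's own timing figure is 2.8 years per batch; (100/6 + 12 + 6)/12 = 2.89 years, which agrees if truncated and is not disputed. Recruiting 400 infants takes 400/6 = 66.7 months, about 5.6 years, so batches follow calendar time. If each batch is processed as it completes, randomisation balances samples within batches but not between them.

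**2. What ComBat does to a zero.** For feature g in run i, with overall mean α, standard deviation σ, and run estimates γᵢ (shift) and δᵢ (scale):

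y* = α + (y − α)/δᵢ − σγᵢ/δᵢ

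A common floor y = c becomes α + (c − α)/δᵢ − σγᵢ/δᵢ, which depends on i. It stays tied across runs only by coincidence.

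In a simulated taxon, a floor of −5 on the log10 scale became −5.0175, −5.0133, −4.9555 and −5.0005 in the four runs, with 78, 78, 86 and 80 absent samples (322 in all). Kruskal-Wallis by run on these former ties gave H = 321 = 322 − 1, the maximum possible (p about 3e-69). Over all simulated taxa, absent samples took four distinct values in 99.98-100% of cases.

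**3. Effect on Mann-Whitney power.** Assumptions not in the documents: four runs of 100, log abundances, run SD 0.7 on log abundance when present, SD 0.03 in prevalence between runs, 22% exposed (the frequency of family smoking and of pets in Table 1), and a 12-point prevalence effect. The last three columns come from a separate simulation at the same prevalences.

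| Taxon prevalence | Uncorrected | After ComBat | Stratified, uncorrected | Repeat: uncorrected | Repeat: ComBat | Repeat: stratified |
|---|---|---|---|---|---|---|
| 10% | 81% | 39% | 82% | 82% | 36% | 82% |
| 20% | 64% | 40% | 64% | 63% | 41% | 64% |
| 40% | 50% | 42% | 48% | 48% | 39% | 46% |

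The loss is 42-46 points at 10% prevalence, 22-24 at 20% and 8-9 at 40%.

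A third simulation used other assumptions: 200 taxa, prevalence 10-50%, 40% exposed in every run, run SD 0.5 in abundance. With no run effect on detection, power fell from 0.76 to 0.57.

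**4. Effect on false positives (nominal 5%).**
- Exposure balanced over runs: 0.04-0.065 after ComBat, so close to nominal.
- Exposure drifting from 30% to 15% (assumed), no true effect: 20%, 15% and 7% at prevalence 10%, 20% and 40%. The repeat, also with assumed drift, gave 23%, 17% and 7%.
- Exposure drifting from 25% to 55% (third simulation, no or modest run effect on detection): 0.21-0.27 after ComBat against 0.05-0.07 uncorrected.
- Adding the exposure to the ComBat model did not help: null taxa were rejected at 0.12-0.13 even with balanced exposure.

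**5. Within-child centring.** If a child's visits share a run, subtracting the child's mean gives (y − ȳ)/δᵢ. The run shift cancels, and a taxon absent at every visit returns to 0 in all runs. Simulated false-positive rates under the 30% to 15% drift fell to 4.6%, 4.1% and 4.9%. Power to detect a stable difference between children, however, was 14%, 6% and 7%, because centring removes that difference.

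**6. The alternative.** The van Elteren test ranks within each run and sums over runs:

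T = Σₖ [Rₖ − n₁ₖ(nₖ+1)/2]/(nₖ+1)

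where Rₖ is the rank sum of the exposed in run k. Zeros stay tied. Type I error was 5-6% in the first simulation, about 5% in the repeat, and 0.034-0.065 in all nine scenarios of the third. Leaving the data uncorrected and ignoring run is not enough: plain Mann-Whitney reached 0.29 with exposure drifting from 10% to 70% and a large run effect on detection.

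**The case against.** A reader might infer that ComBat will be applied to every dataset. The text does not say so: each dataset is examined first, and correction follows only if required. The microbiome tables may never be corrected.

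A reader might also infer that false associations are to be expected. The documents show no exposure whose frequency changes between runs; the drift values are assumptions. With balanced exposure the error rate stays near nominal.

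Further points are fair:

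- The correction sentence pairs ComBat with within-child normalisation, which removes the false positives.
- The harm needs log or relative abundances. The article gives no scale, and after a centred-log-ratio transform the excess was negligible.
- That Mann-Whitney runs on ComBat output is inferred from the order of the text.
- Mann-Whitney belongs to the cross-sectional tool. LongDat handles longitudinal data, so it would be too strong to say that Aim 3 as a whole depends on this screen.
- A check for artifacts is promised, and zeros split by run would be visible to anyone who looked.

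These points narrow the concern but do not remove it. Centring does not serve a cross-sectional screen of levels, because it takes out the differences sought; that screen needs uncentred data, where the zeros remain split. The artifact check offers no other method to turn to. Storage time is carried as a covariate, but with the batch rule as described its range repeats in each batch, so it cannot stand in for run. Run itself is not named in the nested models.

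**Conclusion.** The point holds conditionally. If 16S or metagenomic data are judged to need correction, the named method is unsuitable for log or relative abundances that feed a between-child rank test. The splitting of tied zeros follows from the form of ComBat and does not depend on simulation settings.

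The main cost is power for sparse taxa: about 82% to 36-39% at 10% prevalence, and much less at 40%. Inflated false-positive rates need exposure to differ between runs. Batches that follow some 5.6 years of recruitment make that plausible, but nothing in the article establishes it. All the rates rest on assumed prevalences, run effects and exposure frequencies, and on the rank screen using ComBat output. Because the article fixes a method that suits some listed layers and not others, this is more than a detail left to a fuller plan.

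**What to change.** Limit ComBat to approximately continuous layers: proteome, metabolome and normalised expression. For 16S, metagenomic and other zero-heavy data, such as lymphocyte receptor repertoires, leave zeros tied and carry run in the analysis:

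- a run-stratified (van Elteren) rank test in place of plain Mann-Whitney for the screen;
- run as a covariate or random effect in the nested linear models and the longitudinal models.

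Carry run whether or not exploratory analysis finds a batch effect.

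The change affects analysis wording only and needs no new samples or assays. The models become slightly longer. In the simulations at 10%, 20% and 40% prevalence, the stratified test had power within 2 points of the uncorrected Mann-Whitney test.

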### Aim

The MIAI study hypothesizes that: (i) the course and outcome of RVIs among individuals is related to the large variability in maturational trajectories of anti-viral immunity and (ii) environmental, lifestyle and dietary factors influence the early imprinting of anti-viral immunity in ways that either promote an increased susceptibility to RVIs and their complicated course or support protective patterns (**Figure 1**). To verify these hypotheses, the MIAI birth cohort has been set up and includes healthy newborn infants born at term and their families. We aim at a comprehensive characterization of age-related differences and changes in the human immune system of the participants with a focus on the function of the cellular key players involved in the establishment of infections with RSV, IAV and SARS-CoV-2. Detailed phenotyping including factors potentially promoting and confounding the individual immune trajectory will be established; in particular, we are interested in the role of the developing microbiome on priming and regulating anti-RVI immunity. The specific aims of our study are:

Aim 1. To characterize the developmental changes of innate and adaptive immune responses to RVIs during the first year of life.Aim 2. To determine the impact of sociodemographic background, clinical histories and environmental factors like lifestyle, vaccinations and dietary factors on the trajectories of immune responses toward RVIs.Aim 3. To elucidate whether there is a link between the microbiome establishment and anti-RVI immunity developing after birth.

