The first study visit is performed at the University Hospital for Women`s health and Obstetrics Würzburg. Mothers of eligible infants are approached in the first three days after birth. After obtaining written informed consent from the parents, the baseline assessment takes place during the hospital stay of mother and infant. The follow-up appointments are performed one month, six months and one year after birth at the dedicated Pediatric Clinical Study Outpatient Service at the University Children’s Hospital Würzburg. We are planning to track the study participants for long-term follow-up during childhood.

Overall, the acceptance of our study design with its follow-up appointments and sample collection is high with a relatively low drop-out rate of about 8% after one year as of May 2024, including families that relocated outside of Würzburg and its administrative district. The baseline characteristics of infants enrolled so far are presented in **Table 1**. Overall, the proportions of female and male infants are equal and the mean gestational age and birth weight appropriate and in line with the inclusion criterium of full-term birth. The largest number of neonates was born vaginally (VD, 62%). Cesarean sections (CS, 38%) were in the majority of CS secondary (60%), i.e. after rupture of membranes, and only a minor part elective (37%) or due to emergency (3%). Half of the MIAI infants have older siblings which of 86% are visiting child care or school. The exposure to nicotine due to smoking family members affects 22% of the MIAI infants and 22% of the families have pets. The distribution of rural compared to urban living environments is even.

Characteristic values of pregnancy histories from infants enrolled in MIAI including maternal factors potentially impacting on the child’s RVI immunity are listed in **Table 2**. The mean weight gain during pregnancies was 14 kg with a mean body mass index (BMI) of 29.4 (± 5.8) at birth, not exceeding the limits recommended by obstetricians (41). The smaller number of mothers were primigravida (38%). During routine prenatal screenings, gestational diabetes mellitus was detected in 12% and gestational hypertension in 1.8%. The proportions of mothers vaccinated and/or recovered from IAV and SARS-CoV-2 infections are 48% and 97%, respectively. For the Influenza status, 52% of mothers did not know whether they have experienced an IAV infection, while only 3% of mothers did not know their SARS-CoV-2 status.

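### A within-child transformation is listed as batch correction without being limited to change-over-time questions; where its output is used between children, constant exposure effects vanish and visit-wise contrasts are distorted

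*Protocol article*

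**What the plan says.** All of this is in the protocol article.

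- **Data analysis and statistics, correction step.** Correction is conditional and decided per dataset: "Subsequent exploratory analyses will determine the necessity of batch correction for each dataset. If required, corrections will be implemented using ComBat batch method". In the same sentence the method is paired with the "WithinVariation function implemented in the R mixOmics package and to normalize features as change over time within each child".
- **Same section, safeguard.** "Post-correction, we will validate that the biological variability is preserved and that no artifacts were introduced". No criterion is given for this check.
- **Same section, what follows.** Subgroup identification by co-expression networks, KmL trajectory clustering, metadeconfoundR and LongDat are described next. metadeconfoundR is presented as a tool for cross-sectional data that first tests features against metadata with nonparametric tests such as Mann-Whitney. The input scale (uncentred or within-child) is not stated for any of these.
- **Aim.** Aim 2 is "To determine the impact of sociodemographic background, clinical histories and environmental factors like lifestyle, vaccinations and dietary factors on the trajectories" of immune responses. Aim 3 asks about a link between microbiome establishment and immunity developing after birth.
- **Nasal brushes.** The airway epithelial infection models are to describe each participant at two ages, birth and one year. The Discussion makes the airway epithelium and blood monocytes the first research focus.

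**The concern.** ComBat and the within-child step do different jobs. ComBat removes differences between analytical runs. Expressing a feature as change within the child removes that child's own level, which is not a batch artefact. Much of what separates one infant from another sits in that level.

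Several planned analyses compare children with each other: exposures fixed at birth (mode of delivery, sex, maternal history), the cross-sectional feature-metadata tests, and endotypes that may differ by level. If these receive the transformed values, a lasting difference between cesarean and vaginally born infants would be reported as no effect. A difference that grows or fades could appear at the wrong visit or with the wrong sign.

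Because the step is decided dataset by dataset, the same constant effect could be visible in one omics layer and erased in another purely through a batch decision. That would undermine the planned integration across layers.

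**Working it through.** The article gives no alpha, power or effect size and states that the sample size is not calculated, so there is no figure of its own to reproduce.

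**Inputs from the article.** Target of 400 infants with full series ("We aim at subjecting full longitudinal sample series from 400 infants to study the omics profiles"). Four visits: birth, then 1, 6 and 12 months. Cesarean share 38%, hence 152 exposed and 248 unexposed out of 400. Current cohort 171 (65 cesarean, 106 vaginal; Table 1).

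**Assumptions not in the article.** Effect sizes of 0.3 or 0.4 SD, total SD 1, intraclass correlation (ICC) of 0.3, 0.5 and 0.7, two-sided tests at 0.05. Change within each child is taken as deviation from the child's own mean; subtraction of the birth value is considered where it matters.

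**Step 1, algebra.** For child i at visit t, let y = a + d·x_i + g·x_i·f(t) + b_i + m(t) + e_it, where x_i is a birth-fixed exposure. Subtracting the child's mean leaves g·x_i·(f(t) − mean f) + (m(t) − mean m) + (e_it − mean e). The level effect d and the child effect b_i cancel exactly. They also cancel if the birth value is subtracted. The exposure-by-time effect g remains.

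**Step 2, visit-wise contrasts after mean-centring.**
- Effect growing linearly from 0 to 0.4 SD: its mean over visits is 0.4 × (0 + 1/12 + 1/2 + 1)/4 = 0.158. The birth difference becomes 0 − 0.158 = −0.158 (truth 0), and the 12-month difference 0.4 − 0.158 = 0.242 (truth 0.4).
- Effect fading linearly from 0.4 SD to 0: its mean is 0.4 × (1 + 11/12 + 1/2 + 0)/4 = 0.242. The 12-month difference becomes −0.242 (truth 0).
- If the birth value were subtracted instead, the birth contrast would be 0 by construction and each later contrast would be a difference in change. In the fading case the 12-month contrast would be 0 − 0.4 = −0.4.

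**Step 3, simulation.** 400 infants (152 vs 248), 500 runs per setting, ICC 0.3 to 0.7, mean-centring. Estimates are followed by the rejection proportion, as a range over the three ICCs.

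| True effect | Contrast | Uncentred | Centred |
|---|---|---|---|
| Constant 0.4 | Child mean | about 0.40 (0.996–1.00) | exactly 0 |
| Constant 0.4 | Birth or 12 months | 0.39 to 0.42 (0.96–0.98) | about 0 (0.036–0.064) |
| Growing to 0.4 | Birth | about 0 (0.036–0.054) | about −0.16 (0.53–0.91) |
| Growing to 0.4 | 12 months | about 0.40 (0.97–0.98) | about 0.24 (0.87–1.00) |
| Growing to 0.4 | Slope over 12 months | about 0.40 (0.94–1.00) | identical |
| Fading from 0.4 | 12 months | about 0 (0.03–0.05) | about −0.24 (0.92–1.00) |
| Fading from 0.4 | Slope over 12 months | about −0.40 (0.96–1.00) | identical |

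**Step 4, what a constant effect could otherwise yield.** With 0.3 SD and ICC 0.5, the variance of a child mean is 0.5 + 0.5/4 = 0.625. At n = 400, z = 0.3/√(0.625 × (1/152 + 1/248)) = 3.68, power about 0.96. At n = 171, z = 0.3/√(0.625 × (1/65 + 1/106)) = 2.41, power about 0.67. After centring, the expected difference is 0 at either size.

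**Step 5, two-visit features.** With only birth (y1) and one-year (y2) values, the centred values are (y1 − y2)/2 and (y2 − y1)/2. They are mirror images: the change survives, and neither level does.

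**The case against.** **The step is conditional.** It applies per dataset and only if required, and the article never says that its output enters every later analysis. This stands, and it limits the point to datasets where the step is applied and its output carried forward.

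**Input scale may be left to the full plan.** A condensed article need not state which dataset enters which tool. This stands in part. Here, however, the article itself names the transformation, calls it batch correction, places it before the subgroup, clustering and association analyses, and states no limit. Followed as written, it would give wrong between-child results.

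**The aims concern trajectories.** A reader might infer that Aims 2 and 3 lose their main signal. The documents do not support that. Aim 2 is worded as impact on trajectories, Aim 3 as developing microbiome and immunity, and slope contrasts are identical before and after centring. Many Aim 2 exposures (vaccinations, infections, antibiotics, diet, day care) are recorded at every visit in Table 4, so within-child contrasts on them remain estimable where they change.

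**The safeguard would catch it.** A reader might infer that the variability check must fail by construction. Without a stated criterion that cannot be said: a check confined to variation over time would pass. A stricter check might flag the loss, but no check restores a level already removed.

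**Dependence after centring.** Centred values sum to zero within each child, and one might infer that later models will wrongly treat them as independent. Nothing in the article says so, and LongDat is described as a longitudinal tool. That inference is not carried forward.

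**Conclusion.** The point holds in limited form. Where the within-child step is applied and its output feeds later analyses:

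- any time-constant effect of a birth-fixed exposure is exactly zero, whatever the effect size, ICC or number of infants;
- visit-wise group contrasts are distorted, by about 0.16 SD in the growing example and about 0.24 SD in the fading one;
- KmL can find differences in shape only;
- the cross-sectional metadeconfoundR tests no longer compare levels between children;
- features measured only at birth and one year reduce to a single change score.

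Exposure-by-time effects and within-child associations are unaffected, so Aims 2 and 3 are impaired in part. The exact zero and the unchanged slope follow from algebra and need no assumption. The distortion figures assume linear patterns reaching 0.4 SD and mean-centring. The power figures (0.3 SD, ICC 0.5) are illustrations and take no account of omics multiplicity.

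**What to change.** Separate the two operations in the analysis plan:

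1. Batch correction uses ComBat, or analytical run as a covariate, and nothing else.
2. WithinVariation output is used only for within-child change-over-time analyses.
3. Between-child analyses (birth-fixed exposures, metadeconfoundR, level-based KmL endotypes) use batch-corrected, uncentred values, with a child random intercept in models of repeated visits.
4. Level and slope effects of each exposure are reported separately.

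The cost is about one paragraph, with no new data or assays. It is best settled before the omics analyses are run.
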